| **Statistical Considerations:** | **Primary Endpoint:**  The primary outcome (proportion of patients with PSMA-positive pathological lesions = patient based sensitivity) will be compared between tracers using an absolute risk difference (new tracer minus old tracer) with a one-sided lower 95% confidence interval for paired proportions (Wald with Bonett–Price Laplace adjustment). If the lower limit lies above -10%, we will claim non-inferiority. Detection rates per patient will be based on majority consensus reads.  **Secondary Endpoints:**   - Parametric imaging will be performed for the two radiotracers in a subset of patients (n=10*), allowing comparison of the tracers’ dosimetric and kinetic parameters, with affinity for the PSMA radioligand by calculation of the parametric equilibrium constant *K*_D,_ which will be compared between the two tracers with descriptive statistics. - The number of PSMA-positive lesions defined as pathological, benign and uncertain per region will be compared using mixed-effects Poisson regression. Patient-level data will also be analysed using the Wilcoxon signed-rank test.. - Inter-reader reliability will be compared on the region level using Krippendorff’s alpha for benign, pathological and uncertain lesions, separately for the two tracers. - Region based PPV will be calculated for each tracer separately with 95% Wilson score confidence intervals. The two tracers will be compared using McNemar’s test and an absolute risk difference with 95% confidence interval. - Semi-quantitative tumour to background ratio (defined as lesion SUV ÷ SUV of reference background region, where the background uptake is defined by convention as the left gluteal musculature) will be summarised on a region-level (i.e. using the mean over all positive lesions per region). Summarised data will be analysed using linear mixed-effects regression models. - The number and severity of adverse event will be analysed using descriptive statistics. All serious adverse events will be listed.   *The requirement for N=10 patients is justified on the previous dosimetry paper for the established PET radiotracer ^68^Ga-PSMA-11 which was adequately powered to demonstrate a mean-effective dose of 0.023 ± 0.004 mSv/MBq, i.e. with a precision in the µSv range [1]. |

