## Clinical Evidence to Date

This investigation for these two radiopharmaceuticals will be the first such head-to-head comparison for this patient group. By definition, no systematic reviews are available. We are aware of no evidence of any reports of adverse safety profile, history of modification or recall of either of the substances.

We note one pilot study comparing these two radiotracers by Kuten et al., albeit in in a small cohort of primary prostate cancer patients and not in recurrent prostate cancer and in a study which did not conform to standard trial methodology [17]. Likewise, a retrospective comparison by Rauscher et al [13] exists, showing no inferiority between ^68^Ga-PSMA-11 PET and ^18^F-PSMA-1007 PET, although no sample size or power estimate was included. Both studies used a two point scale (binary positive/negative) and did not consider the possibility of diagnostic uncertainty, which is an under-investigated phenomenon and which this study seeks to address. A small case series reported increased diagnostic certainty for lesions in close proximity to the bladder with additional ^18^F-PSMA-1007, although we note the lack of diuretics for ^68^Ga-PSMA-11 as major weakness of this study [15]. This will be the first clinical study of prospective, randomised design conforming to standards for evidence-based medicine. The study design incorporates reduction of bladder activity through diuretic use, in-keeping with clinical evidence and guidelines. Diagnostic certainty in these tracers has hitherto been inadequately studied.

We note that PSMA radioligand uptake can be non-specific [16], and that non-prostatic tracer uptake is reported as increased in ^18^F-PSMA-1007 compared to ^68^Ga-PSMA-11 [13]. We consider this latter point to be of high clinical relevance: unnecessary additional diagnostic testing or treatment can result from diagnostically uncertain lesions.

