## Secondary Outcomes

- Intra-individual comparison of the parametric imaging parameter K*_D_* (measure of tracer affinity) for the two radiotracers for n=10 patients.
- The number of pathological, benign and uncertain lesions for each tracer in five regions (prostate bed, pelvic lymph nodes, extra-pelvic lymph nodes, bone, or other organs) classified by six blinded readers (three for each tracer) using previously published interpretation guidelines (PSMA-Rads 1.0)
- Inter-reader reliability between the three readers for each tracer on the level of the region with respect to three categories (pathological, benign, uncertain).
- The region-based positive predictive value (PPV), i.e. the percentage of pathological lesions that are confirmed pathological at the 6 month follow-up (based on the subset of patients and lesions with follow-up data at 6 months).
- Tumour visibility will be compared by means of uptake values (SUV) as well as tumour to background contrast in a lesion based analysis. The tumour to background ratio (TBR) is defined as lesion SUV and SUV÷ SUV of reference background region, where the background uptake is defined by convention as the left gluteal musculature.
- Number and severity of adverse events per tracer (up to 48h follow-up, see below)

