### Imaging Procedures

Imaging will be performed on the same scanner for all patients at the clinic for nuclear medicine, university hospital Bern. PET scans will be obtained using standard parameters for the scanner type. All examinations will be documented as per clinical routine. The trial physicians when reading the scans will be blinded to this report and the clinical details of the patient.

*6.1.2.1 Imaging Protocol*

Patients will receive standard PET/CT acquisitions as per institutional imaging protocol at 2h p.i. For n=10 individuals, additional dynamic imaging will be performed from the time-point of injection to 80 min (dynamic scans)

*6.1.2.2 Details of analysis*

1. A total of 6 readers will be allocated to the study. 3 readers will be allocated to read all scans for one tracer, 3 readers will be allocated to read all scans for the second tracer. This ensures that both radiotracers are interpreted separately. The odd number of readers allows for simple-majority voting in case of disagreement (i.e. where one reader rates the scan as negative and two others positive).
2. All readers will be experienced in reading scans with their respective tracer type (minimum 100 clinical scans). A training set of literature will be provided to all readers before the study commences, informing the reading physicians about potential pitfalls and normal distribution of both tracer types.
3. Visual analysis will be done according to previously published reading criteria (e.g. PSMA-RADS) to include pathological, non-pathological and diagnostically uncertain lesion types [21].
4. Reading will be done by the readers in a blinded, randomised fashion. The scans will be read at independent reading sessions. No reader will have access to the other readers’ results or interpretation.
5. Readers will report the number of lesions by lesion type (PSMA-RADS 1.0) and by region, as described above.
6. Both readers will record tracer uptake (SUV) and determine lesion to background ratio, which is defined as lesion SUV (peak) ÷ SUVmean of background reference region (defined by convention as the left gluteal musculature).
7. The principal investigator and his team will perform an unmasked scrutiny of medical records to 6-months post the second exam. Where available, a composite standard of correlative imaging, histology and prostate specific antigen will be compared affording a descriptive analysis of lesion-based diagnostic accuracy.

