### Primary Analysis

The primary outcome (proportion of patients with PSMA-positive pathological lesions) will be compared between tracers using an absolute risk difference (new tracer minus old tracer) with a one-sided lower 95% confidence interval (CI) for paired proportions (Wald with Bonett–Price Laplace adjustment). If the lower limit lies above -10%, we will claim non-inferiority. Proportion of pathologic scans will be based on majority consensus reads.

The number of PSMA-positive lesions defined as pathological, benign and uncertain in each region will be analysed using separate mixed-effects Poisson regression models with tracer as fixed covariate and nested random effects for patient and region. We will report incidence rate ratios with 95% CI and p-values. As a sensitivity analysis we will compare the number over all regions using the Wilcoxon signed-rank tests and the Mann-Whitney statistic with 95% CI.

Inter-reader reliability will be analysed on the region-level based on the number of benign, pathological and uncertain lesions determined by each reader. We will calculate Krippendorff’s alpha with a ratio difference function and bootstrap 95% CI separately for each tracer.

Lesion-based PPV will be calculated for each tracer as the proportion of pathological lesions confirmed pathological during follow-up among all lesions with a known state and will be presented with 95% Wilson score CI. Using all lesions with a confirmed status during follow-up, the two tracers will be compared using McNemar’s test and an absolute risk difference with 95% confidence interval.

The semi-quantitative tumour to background ratio will be summarized on a region-level (i.e. using the mean over all positive lesions per region) and analysed using a linear mixed-effects regression model with tracer as fixed covariate and patient and region as nested random effects. The mean difference with 95% CI will be reported.

For the subset of patients with additional parametric imaging data (N=10) the planned analysis of parametric imaging parameters (see first secondary endpoint) is planned prior to completion of the study. This exploratory analysis of this secondary endpoint will not assess the primary endpoint and will not influence further trial conduct or further trial process.

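### The lesion-count rate ratio takes its confidence interval and p-value from the two lesion totals alone, so they can be too narrow or too wide

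*Protocol*

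**What the plan says.** Protocol section 11.4.2 plans one model per lesion class: "separate mixed-effects Poisson regression models with tracer as fixed covariate and nested random effects for patient and region". The reported result follows: "We will report incidence rate ratios with 95% CI and p-values". No patient-by-tracer term, overdispersion term, reader term or robust standard error is named.

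A sensitivity analysis is planned in the same paragraph: "As a sensitivity analysis we will compare the number over all regions using the Wilcoxon signed-rank tests", together with a Mann-Whitney statistic and its 95% CI. The synopsis agrees: "Patient-level data will also be analysed using the Wilcoxon signed-rank test".

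Section 5.2 makes the counts a secondary outcome over five regions, "classified by six blinded readers (three for each tracer) using previously published interpretation guidelines". Section 6.1.2 gives each tracer its own group of three readers, who read every scan made with that tracer. Each reader reports counts by lesion type and region. Section 11.4.2 mentions majority consensus only for scan positivity. The protocol does not say how three counts per scan become the model's response.

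**The concern.** Patient and region intercepts describe how many lesions a patient or region has. They do not describe how the difference between tracers varies from patient to patient, and that variation determines the precision of a paired comparison. Under the planned model, ten extra foci in one patient carry the same weight as one extra focus in each of ten patients. A lesion seen on both scans is also treated as two independent events.

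Section 3.4 states "We note that PSMA radioligand uptake can be non-specific", reports more non-prostatic uptake with the new tracer, and regards the resulting uncertain lesions as highly relevant clinically. The rate ratios for benign and uncertain lesions are the main planned estimate on that question. A miscalibrated interval could produce a false tracer difference there, or hide a real difference in pathological lesions.

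**Working it through.** **Plan's own figure.** None is given for this analysis. The nearest calculation is the primary power in section 11.2. Exact enumeration with 100 patients, 80% positive per tracer, 75% positive on both (so 5% + 5% discordant), the Bonett-Price limit and one-sided 2.5% gives 86.5%, against 85% stated. The paired inputs are therefore read correctly.

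**Step 1: standard error of the planned model.** In patient i and region j, let the counts be Poisson with means λij and λij·θ. Given the cell total, one tracer's count is binomial with probability θ/(1+θ), which does not contain λij. The random intercepts affect only the totals. Hence

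- estimate = log(N1/N2)
- SE = sqrt(1/N1 + 1/N2)

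A numerical fit of the nested mixed model to one simulated data set gave estimate -0.0104 and SE 0.0834. The closed form gave the same values.

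**Step 2: when the interval is too narrow.** Assumptions, not in the documents: 100 patients, 5 regions, patient and region log-SDs of 0.8, independent normal tracer deviations per patient with SD 0.5 for each tracer (log-ratio SD 0.5 × √2 = 0.71), and no shared lesions. The mean total is 323 per tracer.

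- Model SE: sqrt(2/323) = 0.079
- Actual SD of the estimate: 0.135
- Ratio: 0.135/0.079 = 1.71, so 1.96 acts like 1.96/1.71 = 1.15, which means about 75% coverage
- Simulated coverage: 75.2%; with fewer lesions (119 per tracer), 86.1%

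**Step 3: when the interval is too wide.** Suppose S of the N lesions on each tracer are seen by both. Shared lesions cancel in the ratio, so without heterogeneity the true variance is about 2(N - S)/N², against the model's 2/N. The SE ratio is sqrt(1 - S/N). If a fraction c of all lesions is seen by both, S/N = 2c/(1+c).

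- c = 0.50: S/N = 0.667, SE ratio 0.577, true SE 0.097 × 0.577 = 0.056 (simulated 0.056; coverage 99.9%)
- c = 0.75/0.85 = 0.88: S/N = 0.9375, SE ratio 0.25, true SE 0.087 × 0.25 = 0.022 (simulated 0.022; coverage 100%)

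The value 0.75/0.85 is section 11.2's joint positivity divided by positivity on either tracer (80 + 80 - 75 = 85%). It is a patient-level figure, borrowed only to indicate high concordance.

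**Step 4: both effects together.** Assumptions: 100 patients, 5 regions, mean 0.6 lesions per region (about 300 per tracer), log-SDs of 1.0 between patients and 0.8 between regions, no average tracer effect, and heterogeneity only in unshared lesions. Type I error of the planned two-sided 5% test:

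| Share of each tracer's lesions seen by both | log-ratio SD 0.25 | SD 0.5 | SD 0.75 |
|---|---|---|---|
| 0% | 9% | 17% | 31% |
| 50% | 0.6% | 3.1% | 8.0% |
| 75% | 0.0% | 0.1% | 0.6% |

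Patient-clustered SEs, sqrt(Σi (yi1/N1 - yi2/N2)²) with yi1 and yi2 the patient's totals, give about 6 to 7% throughout.

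**Step 5: why the response must be one count.** If all three reads were entered as separate rows and the readers saw the same lesions, N would triple and the SE would shrink by 1/√3 = 0.58 with no new information. The protocol does not say that this is intended.

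**The case against.** The strongest objection concerns direction. A reader might infer that the intervals are simply too optimistic and that false tracer differences will be declared far more often than 5% of the time. The documents do not support that. They give no between-patient variance and no lesion overlap. The same patient is scanned twice, 2 to 14 days apart, without a change of prostate cancer treatment, and section 11.2 assumes high concordance. The 9 to 31% figures hold only with no overlap; with substantial overlap the planned test is mostly conservative. This objection stands, and the point is therefore one of miscalibration in either direction.

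The patient-level Wilcoxon and Mann-Whitney analyses do not rely on the Poisson variance and could expose a result driven by a few patients. That also stands, but they are sensitivity analyses and do not repair the interval reported for the rate ratio.

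Two further readings go too far:

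- That the three reads will be stacked. The protocol states no such layout, and an SAP may settle it.
- That a single tracer effect pooled over regions narrows the interval. It is a choice of estimand. It may hide regional differences but does not by itself make the SE wrong.

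**Conclusion.** The point holds as a calibration problem. The written model fixes the SE of the log rate ratio at sqrt(1/N1 + 1/N2), which follows from the model with one count per cell and needs no assumption about variances. The size of the error does depend on assumptions. Type I error is about 9 to 31% with no overlap and a patient log-ratio SD of 0.25 to 0.75. It is 0.6 to 8% at 50% overlap and below 1% at 75%. Too narrow is the more plausible direction for benign and uncertain foci, and too wide for pathological lesions, but the documents prove neither.

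The outcome is secondary, and the primary non-inferiority analysis does not use this model.

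**What to change.** Keep the Poisson rate ratio as the estimate. Base its 95% CI and p-value on patient-clustered robust SEs or on a bootstrap that resamples whole patients. Either corrects both directions. A patient-by-tracer random slope alone does not, because it can only add variance and cannot correct the too-wide case.

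Define the response as one count per patient, region, tracer and lesion class, for example the median of the three reads, and state that reads are not stacked. This does not separate reader from tracer: each tracer has its own three readers, so a systematic difference between the two groups stays in the rate ratio, and patient clustering does not remove it. The report should say so.

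The cost is a small change to the analysis text, with no new data and no change in sample size. Section 11.4.2 already plans bootstrap intervals for Krippendorff's alpha. Intervals may widen or narrow.

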## Determination of Sample Size

Power was determined using Monte Carlo simulations with 1000 repetitions and the following assumptions:

- Marginal probabilities: 80% of the patients are positive for tracer A and 80% are positive for tracer B
- Both tracers are applied to each patient
- Non-inferiority design with a one-sided alpha of 2.5%
- Non-inferiority margin of -10% (clinically acceptable margin in detection rate, balanced against the requirements for clinically realistic number of patients). We justify this margin as being less than 50% of the margin reported for superiority (22%) in a prospective trial published for ^68^Ga-PSMA-11 versus the first-generation tracer ^18^F-Choline [22].
- Non-inferiority is concluded if the lower limit of a 95% confidence interval (Wald with Bonett–Price Laplace adjustment) for the difference in the proportion of tracer-positive patients (new tracer – old tracer) is larger than the non-inferiority margin
- A pragmatic assumption is made regarding the correlation of the paired measurements. Limited data are available for this, given the dearth of comparative studies. Neither retrospective analyses [28] nor limited pilot studies [17, 27] have demonstrated any difference in detection rate. We take a worst-case scenario, and assume that both tracers are positive for 75% of the patients.

Data was simulated using function rmvbin from R package bindata [29]. With 100 patients we will have a power of 85% to detect non-inferiority.

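### The sensitivity analysis of lesion counts pairs the signed-rank test with a Mann-Whitney interval whose usual form ignores that each patient contributes a count for both tracers

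*Protocol*

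**What the plan says.** Section 11.4.2 sets out the main analysis of the numbers of pathological, benign and uncertain lesions as "separate mixed-effects Poisson regression models with tracer as fixed covariate and nested random effects for patient and region". It then adds a check: "As a sensitivity analysis we will compare the number over all regions", using "the Wilcoxon signed-rank tests and the Mann-Whitney statistic with 95% CI".

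The design is a cross-over. The sample-size section (11.2) states the structure directly: "Both tracers are applied to each patient". Each patient therefore has one total count per tracer in each lesion category, and the two counts form a pair.

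The protocol does not say how the Mann-Whitney interval is to be computed. It gives no mean, variance or within-patient correlation for lesion counts. The synopsis, under Statistical Considerations, names only the paired test for this purpose: "Patient-level data will also be analysed using the Wilcoxon signed-rank test".

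**The concern.** The two quantities reported together do not belong together. The signed-rank test works on within-patient differences. The Mann-Whitney statistic compares the two marginal distributions, and its standard interval is derived for two independent groups and has no covariance term. A programmer who follows the text in its ordinary meaning would use an independent-samples routine.

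For positively correlated pairs that interval is too wide. A significant p-value could then stand beside an interval that includes no effect. The comparison of lesion numbers is a named secondary objective (Section 4.3), and Section 3.4 describes the reported excess of non-prostatic uptake with the new tracer as clinically important. An over-wide interval could make a real excess look inconclusive, which weakens its value as a check on the Poisson models.

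**Working it through.** **1. The plan's own figure.** The protocol states no interval width. Its one quantitative statement that depends on the pairing is the power: "With 100 patients we will have a power of 85% to detect non-inferiority". The inputs are "80% of the patients are positive for tracer A and 80% are positive for tracer B" and "assume that both tracers are positive for 75% of the patients". The cells are then 0.75 (both positive), 0.05 and 0.05 (discordant) and 0.15 (both negative). Simulating the Bonett-Price adjusted Wald lower limit against -0.10 with n = 100 and one-sided 2.5% (200,000 repetitions) gives 86.5%. The Monte Carlo standard error of a figure from the protocol's 1,000 repetitions is √(0.85 × 0.15 / 1000) = 1.1 points, so the stated 85% is reproduced. The primary analysis handles the pairing correctly.

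**2. Formula for the interval.** Let X be the count with the old tracer and Y the count with the new one, and let θ = P(Y > X) + ½P(Y = X), taken over all pairs of patients. Let V_i and W_i be patient i's placement values (the average comparison score of his Y against all X, and of his X against all Y).

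- Conventional variance: (S_V² + S_W²)/n.
- Variance allowing for pairing: (S_V² + S_W² + 2·C_VW)/n. The covariance C_VW is negative when the counts are positively correlated.

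With equal variances and a correlation of -ρ between V and W, the width ratio (conventional / paired) is 1/√(1 - ρ):

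- ρ = 0: 1.00
- ρ = 0.4: 1.29
- ρ = 0.5: 1.41
- ρ = 0.6: 1.58
- ρ = 0.8: 2.24

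Here ρ refers to placements, which behave like ranks, so these values match raw-count correlations only roughly.

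The only within-patient dependence that the protocol gives is for the yes/no endpoint: phi = (0.75 - 0.80 × 0.80)/(0.80 × 0.20) = 0.11/0.16 = 0.6875. Put into the rule, it gives 1/√0.3125 = 1.79. It concerns positivity and not lesion counts, so it is orientation only.

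**3. Simulation with counts (distributional assumptions are the review's own).** n = 100 pairs, a gamma-Poisson model with a shared patient rate, no tracer effect, 400 repetitions per setting. The implied correlation is m·d/(1 + m·d) for mean m and dispersion d.

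| Mean, dispersion | Count correlation | Width ratio | Coverage, conventional | Coverage, paired |
| --- | --- | --- | --- | --- |
| 1.5, 0.5 | 0.42 | 1.28 | 98.3% | 94.0% |
| 2, 0.5 | 0.50 | 1.36 | 99.5% | 95.5% |
| 1.5, 1 | 0.60 | 1.47 | 99.5% | 95.8% |
| 2, 1 | 0.66 | 1.59 | 100% | 96.5% |
| 2, 2 | 0.80 | 1.87 | 100% | 94.5% |
| 4, 4 | 0.94 | 2.61 | 100% | 96.3% |

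A second model with a shared log-normal patient effect (log-SD 0.8 to 1.2, mean 1 to 4) gave width ratios of 1.23 to 1.91. Together the two models span about 1.2 to 2.6.

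**4. Disagreement with the test.** Log-normal model, true rate ratio 1.3, 1,000 runs per setting (Monte Carlo error at most about 3 points, 1.96 × √(0.25/1000)):

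- At log-SD 1.2 and mean 2, the width ratio was 1.60. The conventional interval excluded 0.5 in 12% of trials, and the paired one in 47%.
- In 60% of those trials the signed-rank test gave p < 0.05 while the conventional interval still included 0.5. Across the settings this share ran from 25% to 84%.
- Part of this remains with a correct variance. If at least 60% of trials have a significant signed-rank test and the paired interval excludes 0.5 in 47%, the two must differ in at least 60 - 47 = 13% of trials. The test and the statistic measure different things.

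**The case against.** The strongest reply is that the protocol names a statistic and not a variance. P(Y > X) + ½P(Y = X) is a legitimate effect measure for paired data, provided that its variance allows for the pairing. The authors plainly know that the data are paired: the same section uses a paired-proportions interval, McNemar's test and patient random effects. The interval method for a sensitivity analysis is commonly left to the SAP, which is not shown.

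Much of this stands. The excess width is conditional on the conventional interval being used, and the point estimate itself is not wrong. It does not dispose of the point, because the plan names a measure whose standard interval does not fit the design. Elsewhere the same section states the pairing or the interval method: paired proportions for the primary comparison, a bootstrap for Krippendorff's alpha, Wilson score intervals for PPV. Here it states neither.

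A reader might infer more than the protocol supports:

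- **A fixed factor, such as 1.5.** In the gamma-Poisson runs that value needs a count correlation near 0.6, which the protocol does not give. The correlation may also differ between pathological, benign and uncertain lesions, and the separate reader groups for the two tracers (Section 6.1.2) could lower it.
- **A loss of the cross-over's precision in general.** The Poisson models carry a patient random effect and the signed-rank test is paired. Only this one interval is exposed.
- **The same error in the synopsis.** It names only the signed-rank test, which suits the design.

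**Conclusion.** The point holds in a limited form. Read in its ordinary sense, Section 11.4.2 attaches an independent-samples interval to paired counts and sets it beside a paired test. If the conventional interval is used and the within-patient correlation is positive, the interval is about 1.2 to 2.6 times too wide over assumed count correlations of roughly 0.4 to 0.94. Its coverage in the gamma-Poisson runs was 98.3% to 100% instead of 95%. At zero correlation there is no excess. These figures rest on assumed count distributions, since the protocol supplies none.

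The error is conservative: it can hide a difference but does not create false ones. It touches a sensitivity analysis of a secondary endpoint. The non-inferiority decision, the sample size and the main count models are unaffected.

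**What to change.** In Section 11.4.2, replace the Mann-Whitney statistic with a paired effect measure and a 95% interval from resampling patients. There are two suitable choices:

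- the Hodges-Lehmann within-patient difference, which is the direct counterpart of the signed-rank test;
- the within-patient probability that the new tracer shows more lesions, plus half the probability of a tie. It ignores the size of the difference but is easy to read when many counts are tied.

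Alternatively, keep the Mann-Whitney statistic and state that its interval uses a variance or a patient-level bootstrap that accounts for pairing. This corrects the width but, as step 4 of the working shows, does not make the interval agree fully with the signed-rank test. The first option is therefore preferable.

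The synopsis needs no correction on this point. The cost is one sentence in the protocol or SAP and a few lines of code; the design, data collection and sample size do not change.
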